## Abstract

**Introduction:**

According to people with Parkinson’s disease (PD), gait impairments are the most disabling motor symptoms of PD. Recently, motor imagery (MI) has gained notoriety as a gait training technique due to the flexibility of its use, however, it has not been demonstrated that causes a superior effect when included in physiotherapy. This study aims to determine if gait training combined with MI has a greater effect on the gait of people with PD than just gait training.

**Methods:**

The GAITimagery is designed as a double-blind, randomized control trial, including a convenience sample in 2 parallel groups (1:1) with two interventions of 2 sessions per week during 6-week and 8-week follow-up. The initial recruitment will be 88 participants with idiopathic PD and unimpaired cognition state, who will be randomly divided into two groups: GAITimagery (GiG) or the active control Gait group (GaG). Both will perform the same gait exercises but only GiG will include MI training. Gait speed is the primary outcome, while Maximum gait speed (m/s) and Gait speed variability are the secondary results. The tertiary outcomes are related to Quality of life, Daily life activities, Freezing of gait, Balance, Mobility, and Gait performance measures to psychometrics and biomechanics instruments. All results will be measured at baseline (t0), post-training (t1), and follow-up assessment (t2) 8 weeks after finished physiotherapy programs.

**Discussion:**

The GAITimagery program standardizes the application of MI exercises related to the improvement of parkinsonian gait at the same time that monitoring the vividness referred by the participants session by session. The effectiveness of this MI-exclusive program includes subjective and objective measurement tools to detect minimal changes after training. This still-to-be-finish study will support the therapeutic decisions on whether or not to allocate session time to imagery exercises depending on the effect size achieved and the comparison with a control gait training.

## Introduction

1

Parkinson’s disease (PD) is a neurodegenerative, chronic, progressive, and multisystemic disease, with motor and non-motor signs, which affects functional mobility and eventually causes disability and dependence (1, 2). Although the main therapeutic strategy is pharmacological, the effectiveness of oral Levodopa is reduced as the disease progresses (3) and the long-term use has secondary effects (4). On the other hand, physiotherapy is decisive in extending the time of functionality and independence (5), and avoiding major complications such as falls, hospitalizations, and greater overall deterioration (6). Accordingly, patients report gait impairments as the most disabling motor symptoms of the disease (7), which can appear from early onset onwards (8), thus, new gait physiotherapy strategies are continually under study. Recently, motor imagery (MI) has gained notoriety due to the flexibility of its use. MI is the mental rehearsal of action in the absence of overt motor output (9, 10), which may be differentiated into visual motor imagery (VMI) and kinesthetic motor imagery (KMI). VMI relates to the generation of visual representations of motion, while KMI relates to the sensations associated (11). MI is based on activating similar cortical networks as motor execution (11, 12), which would allow people with motor disorders to facilitate the practice of normal movement patterns through MI, as in advanced stages of PD. This premise implies the education of corrected movement along the MI training, to perform the mental practice with a non-altered execution. Related to this, Action Observation (AO) usually is part of MI programs, since observing a scene in motion without moving support learning and accuracy of MI (13).

Previous authors have studied through randomized controlled trials, the effectiveness of MI interventions in PD combined with gait exercises or regular physical therapy (14–17), dual-tasks (18–20), virtual reality (21, 22), and neurofeedback (23, 24). From those works that compare gait training or conventional physical practice with MI versus without MI, they report no differences post-training between groups in motor function after 24 sessions (17), 12 sessions (14), 6 sessions (16), and a single training session (15). Although these designs would allow it to analyze the proportion of improvements attributed to the MI technique, there are methodological considerations that may condition the previously mentioned results. The first of them, is the PD severity presented by the participants in the informed works, which ranges from mild to moderate. Although gait alterations can be observed from the initial stages of PD (8, 25, 26), these may be insufficient to show significant differences between groups post-training. Regarding to this, the non-instrumental measurement tools used (14, 16, 17) may be inadequate to detect small changes when participants do not present severe gait impairments. On the other hand, authors who include MI in gait physiotherapy and use biomechanics assessment tools, only report the effects of a single therapy session (15), therefore a minimum training dose is not given (27) that allows differences to be observed.

Another reason that may contribute to the fact that no differences are observed between therapy with and without MI is the non-stratified randomization of the participants (14–17), since decompensated groups could mask a possible superior effect of the gait physiotherapy supported by MI. Finally, and related to the sample size analyzed in the literature, these do not exceed 50 subjects (14–17), hence the sample size may underestimate the number of participants necessary to observe differences between groups if this is based on intragroup post-intervention change (14). Given the above, this study aims to determine the effect of adding MI exercises to gait training of people with mild-to-severe PD. We hypothesize that MI added to gait rehabilitation achieves a greater effect than isolated gait training in people with PD, and that this effect increases as the disease progresses, even when AO and walking exercise are exactly the same in control and experimental group.

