#### Intervention

2.2.2

Two physiotherapy programs, GAITimagery and gait physiotherapy program, have been scheduled to take place over 6-week period. Each program involves two non-consecutive sessions per week, lasting 60 min each, which makes a total of 12 sessions. Additionally, this study proposes an 8-week follow-up period, which extends beyond the intervention phase. The rationale for this design is based on evidence that the benefits of gait exercises for PD emerge rapidly and are sustained over time, achieving short-term improvements in 12 to 14 training sessions over 2 to 4 weeks (27), which can persist for 3 to 12 months after treatment completion (30). The GAITimagery program will be performed for the GiG, while the GaG will develop the gait physiotherapy program without the MI exercises. To replicate the same conditions in both programs, the sessions will be done in groups of two people with the same PD severity according to the Hoehn & Yahr (H&Y) scale. Each program will be developed by different physiotherapists with an assistant, and supervised by a third physical therapist who checks that the walking exercises applied in both groups are the same. The sessions of both programs also have the same structure: warm-up (10′), central phase (45′), and cool-down (5′). Both interventions will be performed in a quiet environment, in a 7x13m room located in an area isolated from outside noise to promote the concentration of participants during the sessions. The warm-up and cool-down are the same in both programs. The essential aspects of physiotherapy in PD will be included in the warm-up section, related to respiratory exercises, dissociation of the shoulder and pelvic girdle, transfers and postural changes, joint mobility, balance, and strengthening (31). The cool-down part cover self-assisted stretching.

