The central phase includes the gait training itself, in which the first 5′ will be dedicated to the explanation the session objectives and to applying the observation part of AO technique through previously prepared videos of Parkinsonian and normal gait. The purpose of AO in our protocol is to prepare participants who will subsequently perform MI exercises. However, as AO may have an effect on the physical performance of gait exercises by itself (32), both groups will perform the observation part at the beginning of gait training (Figure 2). Within the stipulated 5′, a laptop will be used to show a video focusing on the gait characteristic to be worked on in the session (whether spatiotemporal or kinematic), performed by a subject without pathologies. The physiotherapist will support the visual information with a theoretical explanation of the video content. Next, a video of the same characteristic will be shown but performed by a person with PD. The physiotherapist will explain to participants the features to be corrected. Finally, three additional videos will be shown where participants must say whether it corresponds to a normal or altered pattern. The active part of the AO will be carried out through the gait exercises proposed for each session. The walking exercises for both groups are related to the spatiotemporal and cinematic impairment of the Parkinsonian gait (31), hence are the following (33, 34): (1) step length increase through visual cues and circuit with obstacles of different sizes; (2) cadence control with digital metronome; (3) speed training over 1.00 m/s controlling the stride length and cadence; (4) posture correction during walking; (5) arm swing and shoulder girdle dissociation with proprioceptive and auditory cueing; (6) promotion the lower limb kinematic milestones of stance and swing phase, and (7) Dynamic balance during gait. All the gait exercises will be adapted to the severity of PD.

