**Figure 2 fig2:**

Organization of the GAITimagery and control gait program session. Both programs have the same structure with the exception of the Relaxation and Motor imagery section, which will be only performed in the GAITimagery program. AO, action observation. MI, motor imagery.

Additionally, the GAITimagery program consists of interspersing the physical exercise of walking with periods of MI in each session. Before MI practice, a relaxation exercise will carried out in supine position on a stretcher, obtaining in each session two complete cycles of 2’ of relaxation, 8′ of MI, and 10′ of physical walking exercise related to the treatment objective that is reinforced in the MI period (Figure 2). The MI exercises will consist of imaging a normal gait sequence focused on visualizing a requested movement (VMI) alternating with the focus on the sensation and muscle contraction associated with performing the movement indicated (KMI). MI and relaxation exercises will be guided by the voice of the physiotherapist, who will indicate what movement to imagine and the execution that should be evoked, based on the correction of the gait parameters previously studied in the AO period. All the instructions will be standardized and the physiotherapist will read it from a script. When the goal session is kinematic aspects of gait, the physiotherapist will simply describe to the participants the movement they should imagine, helping them to create a mental image with sufficient detail. When the session’s goal involves speed training, the vocal guidance will include a cadence of the steps, set by a digital metronome that the physiotherapist will listen to through headphones. Between the 8′ of MI guided by the physiotherapist, 30-s spaces will be given without vocal guidance so that participants can silently visualize the required exercise. In this no-guided MI interval, the imagery activity will be monitored through a question about the performance (35), to check the precision of MI (“What moment of the action indicated are you in right now?”). Additionally, at the end of each MI block, the participant will give feedback through two Likert-type questions (36, 37) related to the MI exercise performed (“How difficult was it to visualize the imagery exercise you just completed?” and “How difficult has it been to experience the sensations evoked in the imagery exercise you just performed?”) (Figure 3).

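### The Introduction describes motor imagery added to identical walking, but the session schedule tests imagery in place of part of the walking time

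*Protocol article*

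**What the plan says.** The Introduction gives the aim: "this study aims to determine the effect of adding MI exercises to gait training of people with mild-to-severe PD". The hypothesis that follows is that adding MI to gait rehabilitation does better than gait training alone, "even when AO and walking exercise are exactly the same in control and experimental group".

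Section 2.2.2 (Intervention) fixes the timetable for both arms, the GAITimagery group (GiG) and the control Gait group (GaG):

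- Dose of contact: "Each program involves two non-consecutive sessions per week, lasting 60 min each, which makes a total of 12 sessions".
- Layout: "The sessions of both programs also have the same structure", namely 10 minutes of warm-up, 45 of central phase and 5 of cool-down.
- Central phase: "The central phase includes the gait training itself". Its first 5 minutes are explanation and action observation (AO), and "both groups will perform the observation part at the beginning of gait training".
- GiG then runs two cycles, each with 2 minutes of relaxation, 8 of MI and 10 of walking.
- Figure 2 legend: "Both programs have the same structure with the exception of the Relaxation and Motor imagery section, which will be only performed in the GAITimagery program".

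No sentence gives GaG's walking minutes. A third therapist checks that the walking exercises match between arms; duration is not mentioned. The Discussion paragraph of the Abstract frames the decision differently from the Introduction: whether session time should be given to imagery.

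**The concern.** Adding MI to an unchanged walking programme and replacing part of the walking with MI are two different treatment questions. The Introduction poses the first. With session length equal in both arms and 20 minutes of GiG's central phase taken by relaxation and MI, the schedule points to the second.

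The protocol applies the relevant logic to observation: it gives AO to both arms "as AO may have an effect on the physical performance of gait exercises by itself". It does not apply that logic to walking time, although section 2.2.2 rests its dose rationale on the benefit of gait exercise, and the Introduction names insufficient training dose as one reason why an earlier study may have missed a difference.

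At stake is what the trial may conclude. The Introduction reports that earlier trials comparing training with and without MI found no difference between groups, and this trial is meant to settle whether that reflects MI itself or the methods used. A further null would be hard to read if the arms also differ in the amount of walking.

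**Working it through.** **Inputs** (all from section 2.2.2 and the Figure 2 legend): 2 sessions a week for 6 weeks; session of 10 + 45 + 5 minutes; 5 minutes of explanation and AO at the start of the central phase; GiG cycle of 2 + 8 + 10 minutes, performed twice; relaxation and MI in GiG only.

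**1. The plan's own totals.** 2 × 6 = 12 sessions and 10 + 45 + 5 = 60 minutes. Both agree with the text.

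**2. Time left after AO, either arm.** 45 − 5 = 40 minutes.

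**3. GiG.** 2 × (2 + 8 + 10) = 40 minutes, so the phase is fully accounted for: relaxation 2 × 2 = 4, MI 2 × 8 = 16, walking 2 × 10 = 20. Relaxation and MI together take 4 + 16 = 20.

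**4. GaG.** Walking + any other content = 40. The text names no other content. If there is none, walking is 40 minutes; this is the upper limit.

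**5. Over the programme.** GiG: 12 × 20 = 240 minutes. GaG: up to 12 × 40 = 480 minutes. The ratio is up to 480 / 240 = 2.

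**6. Can the three statements hold together?** Take (a) equal 60-minute sessions, (b) relaxation and MI as the only structural difference, and (c) the same amount of walking.

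| Kept | Consequence for GaG | Statement broken |
|---|---|---|
| (a) and (b) | walks 40 minutes, GiG 20 | (c) |
| (a) and (c) | walks 20 minutes, 40 − 20 = 20 minutes of undescribed content | (b) |
| (b) and (c) | central phase 5 + 20 = 25 minutes, session 10 + 25 + 5 = 40 minutes | (a) |

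Each pair excludes the third, so one statement has to change whichever reading is correct.

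**7. What the between-arm difference measures.** Let *m* be the gain from relaxation and MI, and *w* the gain from GaG's extra walking, up to 20 minutes per session. The expected difference GiG − GaG is *m* − *w*. If extra walking does no harm (*w* ≥ 0), a positive difference implies *m* > *w* ≥ 0 and understates *m*. A difference near zero fits *m* = *w* = 0, and equally *m* = *w* > 0. The documents give no value for *w*.

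**The case against.** The strongest reply is that GaG's 40 minutes appear nowhere. They are a residual, and Figure 2, which sets out the sessions of both arms, cannot be seen here. The legend could be read as GiG's session with the MI section removed, leaving the same two 10-minute walking blocks; rest or instruction between blocks might not count as a section. It would therefore be too strong to infer that the protocol states 40 against 20 minutes. That part of the reply stands, and the figures above are upper limits. It does not remove the problem: under that reading, 20 minutes of GaG's stated central phase have no described content, and the legend's single exception is incomplete.

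Second, sameness may fairly refer to the type of exercise, which is what the third therapist checks. This too is reasonable. But the Introduction's wording, joined to the idea of adding MI, tells a reader more than type.

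Third, a time-matched substitution is a legitimate design, and the Abstract asks that very question. Agreed. A reader might infer that the design is invalid; it is not. The fault lies in describing it as an add-on.

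Fourth, a reader might infer that the sample is too small because lost walking shrinks the effect. The documents do not support this. Section 2.2.4 ties its effect size of 0.15 to the expected difference between the two groups, which may already be net of any walking difference, and no dose-response for walking time is given. No error in the total of 74 is shown.

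Covariate adjustment does not rescue the add-on reading. The Discussion lists sessions completed, medication timing, severity, sex and daily activities. Scheduled walking minutes are not listed and, being fixed by arm, could not be separated from MI anyway.

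**Conclusion.** The point holds as an inconsistency between the stated aim and the schedule. GiG's 20 minutes of walking per session (240 over 12 sessions) follow directly from the text. GaG's figure, up to 40 per session and up to 480 in total, is inferred on the assumption that the central phase after AO holds only walking, which is all that the text names.

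On that assumption the trial answers whether part of the walking time is better spent on relaxation and MI. It does not answer whether MI helps on top of an equal amount of walking. A positive result would be a conservative answer to the Introduction's hypothesis, provided that extra walking is not harmful. A null would leave that hypothesis unresolved. The size of any offset cannot be derived from the protocol.

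**What to change.** 1. Restate the aim and hypothesis in the Introduction as reallocating 20 of the 40 central-phase minutes after AO to relaxation and MI, at equal session time.
2. Limit the claim that the arms are exactly the same to exercise type and AO.
3. State GaG's walking minutes in section 2.2.2.
4. Prespecify that a null result means no net gain from reallocating the time, and will not be reported as showing that MI has no effect.

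If Figure 2 shows non-walking filler in GaG, correct the legend instead and describe the filler. The comparison is then MI against that filler at equal walking time.

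The cost is wording only: no change to patients, visits, staff or sample size. The real price is that the trial gives up the claim to isolate MI's own effect, including the wish at the end of the Discussion to know how much of the gait improvement MI explains. Cutting GaG's walking to 20 minutes and filling the rest with scripted content free of imagery would keep the add-on hypothesis. But it would halve the control training if the inference is right, needs content that may not be inert, and drops the Abstract's practical question. That is a choice for the investigators and is not required to correct the inconsistency.

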## Methods

2

### Study design

2.1

The GAITimagery is designed as a double-blind, randomized control trial with 6 weeks of intervention (two sessions weekly) and 8 weeks of follow-up. The study considered a convenience sample (specifically, modal instance sampling) in two parallel groups (1:1), and an additional matched-healthy group (Figure 1). This protocol used the Standard Protocol Items for Randomized Trials (SPIRIT) guidelines (28) (Supplementary material 1) and the Consolidated Standards of Reporting Trials statement for randomized controlled trials (29) as a guide to be designed. The Human Research Ethics Committee of the Experimental Research Ethics Commission of the University of Valencia approved all the procedures with the number 1557673 (Supplementary material 2) on 11 February 2021. Then it was registered on ClinicalTrials.gov with the number NCT04788693.

**Figure 1 fig1:**
[figure not shown]
Trial design and participants flow. Flow of the study intervention and assessment.

This study will be started with a baseline assessment session (t0) followed by random allocation to one of two study groups: the GAITimagery group (GiG) or the active control Gait group (GaG). The first one will perform 6-weeks of gait physiotherapy combined with MI. The second one will perform the same gait exercise of GiG without the MI techniques. At the end of the interventions, a post-training evaluation (t1) will be carried out, and subsequently, a follow-up assessment (t2) 8-weeks after the physiotherapy programs have finished. Additionally, a third group of healthy matched-sex and age participants will be assessed to compare the performance of PD participants.

### Participants, interventions, and outcomes

2.2

#### Setting and eligibility criteria

2.2.1

Participants will be recruited from the local hospitals and rehabilitation centers of the city of Valencia. The eligibility criteria assessment, obtaining informed consent (Supplementary material 3), assessments, and intervention of both groups will be carried out in the facilities of the Physiotherapy Department at the University of Valencia. The recruitment and eligibility criteria assessments will be accomplished by a neurologist from the hospitals who regularly carry out pharmacological and disease supervision. The inclusion criteria are: (1) diagnosed with PD according to the United Kingdom Parkinson’s Disease Society Brain Bank diagnostic scale; (2) independent walk in a 10-meter corridor; (3) normal cognitive state, determined by the Mini-Mental State Examination with a score ≥ 25 and the Montreal Cognitive Assessment ≥26; and (4) stable medication from the month prior to the start of the study until the t2 assessment. Likewise, the exclusion criteria are: (1) additional neurological condition different from PD; (2) disease or musculoskeletal acute alteration that limits mobility or balance; (3) lower extremities asymmetries >1 cm; (4) report pain on the Visual Analog Scale; (5) suffer from blindness, deafness or any other visual/hearing impairment or pathology that may influence the ability to understand instructions and carry them out; (6) significant tremor that may interrupt the MI exercise; and (7) to perform other physical therapies or sports during the trial or in the 2 months before.

We expect patient recruitment to begin in September 2025 and completed in July 2026. All patients are assumed to have completed baseline testing in September 2026. In addition, the recruitment of healthy people counterparts will be carried out once the participation of patients with PD ends, to recruit people with similar characteristics of age, weight, height, and gender. This procedure will be carried out at the local city’s Municipal Senior Activity Center. The inclusion and exclusion criteria are the same for patients, except those related to the PD.

